#### Randomisation

The trial statistician will be responsible for generating the randomisation schedule (stratified for site and conditioning regimen). This will assign a randomisation code to either placebo or the FMT. Participants will be randomised at a ratio of 2:1 (intervention to placebo).

### Study assessments and outcome measures

After consenting to the study, the participants will undergo a baseline assessment, with collection of the following information: UR number, date of birth, sex, height, weight, diagnosis, treatment details, comorbidities, concurrent medications, ECOG performance status.

#### Stage 1 – Safety run in

Safety: Incidence of adverse events (AEs) assessed using the NCI CTCAE v5.0 (when in patient) with focus on treatment emergent adverse events, i.e. those identified to be related to the IP. AEs will be assessed from the time of starting the first course of FMT until 1 month after completion of the second FMT course. These will be assessed daily if the participant is admitted, and weekly when discharged. When an out-patient, assessments will be performed weekly by a member of the study team (phone call to participants). The Safety Monitoring Committee will be responsible for assigning AEs to either the HSCT treatment or IP. If the AE is deemed as probably or definitely related to the IP, they will be defined as a TE-AE.

Adherence/feasibility: Adherence will be defined by the proportion of participants that complete full course of FMT defined by the number of returned (unused) capsules and from participants’ diaries. The IP will be deemed feasible if participants take at least 75% of each course (pre- and post-HSCT).

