### Participants and study recruitment

The HSCT-BIOME trial will recruit eligible participants scheduled for conditioning chemotherapy prior to autologous HSCT for a haematological malignancy (Table 1).

This is a pilot study aiming to recruit N: 51 participants. This will adequately power the study to detect a 40% absolute reduction (80–40%) in the proportion of participants that meet the primary outcome of the study (alpha: 0.05, beta: 0.2, power 80%).

Potentially eligible participants will be identified at multidisciplinary team meetings (MDTs), hospital admissions and outpatient clinics The study will be introduced to the participant by their clinician, and provided with the PICF and the study will be introduced to the participant by their clinician. Between stem cell mobilisation and providing consent for their HSCT, participants will be given the PICF and consent will be collected at the same time as consenting for HSCT.

Once consented to the study, the participant is assigned a Study ID which will be used to identify all study material.

**Table 1 Tab1:** Inclusion and exclusion criteria

Inclusion	Exclusion
1. Age ≥ 18 years	1. Pre-existing gastrointestinal disease including Crohn’s disease, ulcerative colitis
2. Diagnosis of multiple myeloma, lymphoma or another haematological malignancy to be treated with auto-HSCT	2. Unable to swallow capsules
3. Scheduled to receive conditioning chemotherapy (+/- TBI) prior to auto- HSCT	3. Pregnancy
4. Able to provide written informed consent and follow all clinical trial related procedures (translator to be provided for people of culturally and linguistically diverse (CALD) backgrounds)	4. Nut allergy or anaphylactic food allergy
	5. Uncontrolled vomiting or oral mucositis that may impact swallowing (determined by participant) **
	6. Fever (body temp > 37.8oC) **

**Eligibility criteria to be reviewed before post-HSCT FMT intervention

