### Blinding

Stage 1: No blinding (open label).

Stage 2: This will be a double-blind trial. If a participant reaches the primary endpoint (development of severe diarrhoea within 3 weeks post HSCT) investigators will be unblinded. If the participant is receiving placebo, they will be given a rescue course of open-label FMT (30–36 capsules taken over 5–6 days, i.e. 6 capsules, 3 BD). This innovative design enables the evaluation of the therapeutic efficacy of FMT (i.e. impact of FMT on diarrhoea) without compromising the validity of the trial’s primary objective.

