##### Exploratory outcomes

Gut microbiota composition assessed using microbial genomic sequencing performed on longitudinal stool samples.Plasma short chain fatty acid concentrations assessed in longitudinal blood samples.Plasma citrulline (biomarker of mucosal barrier injury) assessed in longitudinal blood samples.Salivayr metabolome and microbiome.

Safety and adherence will continue to be assessed as per Stage 1.

See Table 3 for study assessment schedule.

**Table 3 Tab3:** Study assessment schedule

Assessment	Before prophylactic FMT	After prophylactic FMT	Day of HSCT (day 0)	During in-patient stay	Before recovery FMT	After recovery FMT	Day + 21	1 month after
Patient demographics								
Comorbidities								
Medications								
Diagnosis/treatment details								
ECOG performance status								
Adherence								
Bristol stool chart (BSC)			Daily					
Frequency			Daily					
Body weight				2-3x weekly while an in-patient				
Symptom burden			*	*	*	*		*
Adverse events ^								

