### Follow up

At 1 month after the last FMT capsule is taken, participants will complete a final set of assessments to determine symptom burden and to identify any adverse events that may be related to the FMT. ESAS-r-CS will be completed to determine symptom burden. Adverse events will be reviewed and categorised using NCI CTCAE v5.0. Assessments will be performed over the phone by a member of the study team.

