### Data analyses and synthesis

All qualitative data will be presented as descriptive data (e.g. participant demographics) and compared between groups using a Chi squared test. Study endpoints will be analysed as follows:

Effectiveness: Proportion of participants that meet the primary endpoint. This will be compared between the two arms using a Chi squared test.Safety: The incidence of all treatment-related AEs and SAEs will be compared between the two groups using a Chi squared test.Adherence: The proportion of participants that take all capsules. This will be compared between the two arms using a Chi squared test.Exploratory microbiota analyses: Uptake of the FMT will be determined by bacterial genome sequencing performed on faecal samples collected from participants.

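### AEs after open-label rescue FMT count as placebo events in the between-arm safety test, and the end of AE follow-up is anchored in two ways that can differ

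*Protocol article*

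**What the plan says.** **AE window.** Stage 1 – Safety run in: "AEs will be assessed from the time of starting the first course of FMT until 1 month after completion of the second FMT course". The closing lines of Exploratory outcomes carry this into Stage 2: "Safety and adherence will continue to be assessed as per Stage 1".

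**Final review.** Follow up: "At 1 month after the last FMT capsule is taken, participants will complete a final set of assessments", which include the review of adverse events. The last column of Table 3 is headed one month after, without naming the starting event.

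**Rescue.** Blinding: investigators are unblinded when a participant reaches the primary endpoint within three weeks of HSCT, and "If the participant is receiving placebo, they will be given a rescue course of open-label FMT". FMT-arm participants have no corresponding course. The section does not say whether rescue precedes, overlaps, replaces or follows course 2.

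**Course 2 re-check.** Footnote to Table 1, on the vomiting/mucositis and fever criteria: "Eligibility criteria to be reviewed before post-HSCT FMT intervention". This implies that course 2 can be withheld.

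**Comparison.** Data analyses and synthesis: "The incidence of all treatment-related AEs and SAEs will be compared between the two groups using a Chi squared test". No rule is given there for events after rescue.

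**The concern.** Two things affect the safety comparison.

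First, rescue gives the active product to one arm only, inside the AE window. A rescued placebo participant with an event judged at least probably due to the product has a TE-AE by the protocol's definition, and a comparison by randomised group places it in the placebo column. If FMT causes harm, the placebo incidence rises with it and the contrast shrinks. Safety is a named aim of this trial, so bias toward no difference is the unwelcome direction.

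Second, the two statements of when AE follow-up ends use different anchors. Crude incidence depends on how long each participant is watched, so the anchor must be defined for everyone. It is not clearly defined for participants who miss course 2 or who receive rescue.

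**Working it through.** **Inputs from the protocol.** N = 51, 2:1 allocation, 80% v 40%, alpha 0.05, power 80%; course 1 starts one week before conditioning and lasts 6 days; course 2 lasts 14 days; each course is 36 capsules (course 2: 6 × 2 + 2 × 12 = 36); rescue is 30–36 capsules over 5–6 days.

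**1. The plan's own figure.** Two-sided test, pooled variance, no continuity correction, k = 2, mean proportion (0.8 + 2 × 0.4)/3 = 0.533:

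n(placebo) = [1.960 × √(1.5 × 0.533 × 0.467) + 0.842 × √(0.16 + 0.24/2)]² / 0.4² = (1.198 + 0.445)² / 0.16 = 16.9, so 17.

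This gives 17 + 34 = 51, with power 80.3%. The stated N is reproduced, and the arms are 17 and 34.

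**2. Expected rescue.** Placebo: 0.80 × 17 = 13.6. FMT arm: 0 of 34 by rule.

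**3. Is rescue inside the AE window?** Under the Follow up anchor, yes by construction. Under the Stage 1 anchor, a 14-day course 2 starting on day +1 at the earliest ends no sooner than day +14, so the window closes no sooner than about day +44. Rescue started the day after an endpoint on day +21 ends on day +26 or +27. Rescue given after course 2 would end 5–6 days into the following month. Wherever course 2 is given, rescue and some observation after it lie inside.

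**4. Dilution (illustration).** Let d be the excess AE proportion caused by both FMT courses, r the fraction of it caused by a rescue course, and f the share of placebo participants rescued. Assuming the same background in both arms, the observed contrast is d − f·r·d = d(1 − f·r). The protocol gives no r. If it followed capsule counts, r = 30/72 to 36/72 = 0.42 to 0.50.

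| f | r = 0 | r = 0.42 | r = 0.50 | r = 1 |
|---|---|---|---|---|
| 0.80 (planning rate) | 1.00d | 0.67d | 0.60d | 0.20d |
| 0.40 (if placebo matched the FMT rate) | 1.00d | 0.83d | 0.80d | 0.60d |

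**5. The two end points.** Dates below are assumed where marked; a month is taken as 30 days.

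*Course 2 completed, no rescue:* the last capsule is the end of course 2, so the rules agree. With ANC recovery on day +10 to +16 (assumed), course 2 ends on day +23 to +29 and follow-up on day +53 to +59.

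*Course 2 withheld:* the Stage 1 rule has no end date. Under Follow up, the last capsule falls 2 days before conditioning starts. With conditioning starting on day −6 to −1 (assumed), that is day −8 to −3, and follow-up ends on day +22 to +27. Compared with +53 to +59, this is 53 − 27 = 26 to 59 − 22 = 37 days earlier, in either arm.

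*After rescue:* the result depends on the reading.
- FMT capsule taken as any study capsule, rescue starting the day after the endpoint: the Follow up end moves later by at most 4–5 days if course 2 starts on day +9, 3–4 on day +10, 1–2 on day +12, and 0 on day +14 or later.
- Rescue given wholly after course 2: 5–6 days later.
- FMT capsule taken literally, rescue starting on day +8 (assumed): rescue ends on day +12 or +13 and follow-up on day +42 or +43, which is 53 − 43 = 10 to 59 − 42 = 17 days earlier.

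**The case against.** The strongest reply is that there is only one AE window. Stage 1 has the window wording, Stage 2 inherits it, and Follow up merely schedules a closing phone call. The protocol also uses FMT loosely for study product: adherence is compared in both arms, and Table 4b schedules sampling around the second FMT course without distinguishing arms. On that reading an unrescued placebo participant has a proper end date, and rescue leaves the Stage 1 window unchanged. How AEs after rescue are tabulated could also be settled in an analysis plan that is not shown.

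Much of this stands for the end points. A reader might infer that they diverge for about 80% of placebo participants, so that incidence is compared over clearly unequal follow-up. The documents do not support that. The 80% is a planning rate for reaching the endpoint, hence for rescue; divergence also requires a particular timing of rescue relative to course 2, which is not given. Nor can a spurious difference in AE incidence be attached to it: the sign is unknown, no AE rate is given, and a constant rate of product-related events through the follow-up month is unsupported.

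Two things remain. The Stage 1 window has no end if course 2 is withheld. And the dilution from rescue does not depend on which anchor governs: the article specifies a comparison by group, and that comparison, run as specified, credits events after rescue to placebo.

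**Conclusion.** The concern holds in this form. The main defect is that the stated safety test counts FMT-related events after rescue as placebo events, for up to about 13.6 of 17 placebo participants and none of 34 in the FMT arm. If FMT raises AE risk, the contrast is biased toward no difference. The size depends on the actual rescue rate and on how much risk a rescue course carries; at the planning rate, with risk following capsule counts, about 60–67% of the true excess would remain visible. That figure is an illustration. If FMT adds no risk, there is no such bias.

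The second defect is a gap in wording. The two end points agree in the ordinary case. They fail when course 2 is withheld (26–37 days apart from a completed course on assumed dates), and after rescue they may differ by anything from 0–6 days later to 10–17 days earlier, depending on readings that the text leaves open. Neither defect affects the primary outcome or the sample size.

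**What to change.** 1. Reconcile Blinding, Stage 1 – Safety run in and Follow up to one AE end point, worded in terms of study product and applied to every randomised participant whether or not course 2 or rescue is given. One form is a common day after HSCT for the between-arm comparison, with collection continuing to at least one month after the last study capsule if that is later. Blinding should also state where rescue falls relative to course 2; that choice is for the investigators.
2. In Data analyses and synthesis, base the FMT v placebo safety contrast on AEs before any rescue capsule, taking time at risk into account. Report AEs after rescue separately as open-label FMT exposure, and keep the as-randomised table beside them.

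**Cost.** Wording in four sections, and a few more of the existing weekly calls for some participants. Treatment and sample size do not change. The statistical price is shorter pre-rescue follow-up in the placebo arm: the contrast becomes less precise, and because rescue is triggered by the outcome, the length of that follow-up depends on the outcome. For this reason the as-randomised table should stay.

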**Methods:**

Peri-HSCT FMT (i.e. before and after HSCT) will be administered to eligible participants (adults undergoing autologous HSCT for a haematological malignancy) over two courses, with the first delivered immediately prior to conditioning and the second starting when ANC > 0.8. Following an open-label, safety run in (N = 5), peri-HSCT FMT will be evaluated for its efficacy in 51 participants, randomised 2:1 to FMT or placebo. The primary outcome is the proportion of participants who develop severe gastrointestinal toxicity defined by 3 consecutive days of severe diarrhoea (Bristol Stool Chart 6+), at a frequency of 4 + bowel movements/day within 3 weeks of HSCT. Safety is defined as the incidence of treatment-emergent adverse events (TE-AEs). Tolerability is defined as the incidence of TE-AEs and adherence to FMT.

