### Study objectives and outcome measures

**Table Taba:** 

Objectives	Outcome measures
Determine prophylactic efficacy of FMT on diarrhoea	Proportion of patients that develop severe diarrhoea determined by 3 consecutive days of BSC6 + at a frequency of 4 + bowel movements/day above baseline within 3 weeks of HSCT * Note: BSC and frequency will also be evaluated individually
Determine therapeutic efficacy of FMT on diarrhoea	Duration of severe diarrhoea defined as BSC6 + at a frequency of 4 + bowel movements/day above baseline
Determine clinical impact of FMT	Changes in body weight (kg) Incidence of fever (body temp > 37.8oC) Incidence of blood stream infections Use of supportive care interventions Duration of hospitalisation
Determine safety of FMT	Incidence of TE-AEs
Determine adherence to FMT administration	Number of capsules taken
Determine effect of FMT on mucosal barrier integrity	Plasma citrulline concentrations
Determine colonisation and function of donor FMT	Gut microbiota composition and diversity determined using bacterial genome sequencing on stool samples and SCFA analyses in plasma
Determine changes in symptom burden	ESAS-r-CS

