#### Safety and data monitoring

A Safety Monitoring Committee will be established for the trial, which will include:

Site PIs.Chief investigator.Head of Haematology.BiomeBank representative(s).

The Safety Monitoring Committee will meet quarterly and review recruitment rates, AE data and other logistical aspects of the trial (e.g. budget). When the Safety Monitoring Committee discussion concerns the treatment of individual participants, the Safety Monitoring Committee consultation process will include the treating clinician of the participant concerned. Participation by the trial statistician and BiomeBank representative will be optional. All discussions about a participant and/or their data, once they are enrolled, will be in a de-identified manner.

If the Safety Monitoring Committee identifies a serious Treatment Emergent Adverse Event (TEAE), they have the discretion to stop the trial or withhold the Investigational Product from the participant. This will be discussed and determined by the Safety Monitoring Committee depending on the severity of the TE-AE and its relationship with the Investigational Product.

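### The safety endpoint counts only adverse events attributed to the product, and no all-cause comparison between the randomised arms is stated

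*Protocol article*

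**What the plan says.** The Stage 1 section of the protocol article describes AE assessment "with focus on treatment emergent adverse events, i.e. those identified to be related to the IP". It then gives the operational rule: "The Safety Monitoring Committee will be responsible for assigning AEs to either the HSCT treatment or IP", and "If the AE is deemed as probably or definitely related to the IP, they will be defined as a TE-AE". Timing of onset plays no part in the rule, and an event judged possibly related does not count.

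The same quantity is the safety outcome elsewhere. The Abstract states "Safety is defined as the incidence of treatment-emergent adverse events (TE-AEs". The objectives table lists only "Incidence of TE-AEs" against the safety objective, and the secondary outcomes include TE-AE incidence. The end of the Exploratory outcomes section brings the method into the randomised stage: "Safety and adherence will continue to be assessed as per Stage 1". Under Data analyses and synthesis the between-arm safety test is "The incidence of all treatment-related AEs and SAEs will be compared between the two groups using a Chi squared test".

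Under Safety and data monitoring, the committee's discretion to stop the trial or withhold product is tied to a serious TEAE. The committee is made up of site PIs, the chief investigator, the head of haematology and product-supplier representatives; supplier attendance is optional. Under Blinding, investigators are unblinded when a participant reaches the primary endpoint, and placebo participants who reach it receive open-label FMT.

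**The concern.** Treatment-emergent normally describes when an event starts or worsens, not what caused it. Here the term means attributed to the product, so events judged unrelated or only possibly related drop out before the arms are compared.

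That matters in this setting. The Background lists infection, diarrhoea and mucositis as transplant toxicities, and it names bacterial translocation leading to infection as the perceived risk of FMT in neutropenic patients. The two look alike at the bedside, so case-by-case attribution cannot separate them reliably. A concurrent placebo arm can, because transplant toxicity is balanced by randomisation, but only if events are counted before anyone judges their cause.

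Two distortions are possible. If attribution is equally sparse in both arms, a real excess shrinks. If attribution depends on knowledge of the arm, the contrast is biased, and the direction cannot be predicted.

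**Working it through.** **The plan's own figure.** Inputs from Participants and study recruitment and from Randomisation: 80% versus 40%, alpha 0.05, power 80%, ratio 2:1. With pooled variance, two-sided, no continuity correction, and p̄ = (17 × 0.8 + 34 × 0.4)/51 = 0.533:

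n(placebo) = [1.96 √(1.5 × 0.533 × 0.467) + 0.842 √(0.8 × 0.2 + 0.4 × 0.6/2)]² / 0.4² = 16.9, rounded up to 17.

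This gives 17 + 34 = 51, as stated. The sample size is not in dispute and does not change.

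**Share of participants unblinded.** At the planning rates, 17 × 0.8 = 13.6 placebo and 34 × 0.4 = 13.6 FMT participants reach the primary endpoint. That is 27.2/51 = 53%. It counts participants, from the moment they reach the endpoint. It is not the share of AEs judged unblinded.

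**Effect of the filter (assumed rates, none from the document).** If a true event rate is p and a fraction q of events is attributed to the product, the analysed rate is q × p. Power is by exact enumeration of two binomials (17 and 34) with the uncorrected chi-squared test at two-sided 0.05.

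| True placebo vs FMT | Attributed (placebo, FMT) | Analysed rates | Power |
|---|---|---|---|
| 30% vs 50% | all events | 30% vs 50% | 29% |
| 30% vs 50% | 1/4, 1/4 | 7.5% vs 12.5% | 4% |
| 30% vs 50% | 0, 1/4 | 0% vs 12.5% | 12% |
| 30% vs 50% | 0, 1/2 | 0% vs 25% | 78% |
| 20% vs 60% | all events | 20% vs 60% | 82.7% |
| 20% vs 60% | 1/2, 1/2 | 10% vs 30% | 32.9% |
| 20% vs 60% | 1/4, 1/4 | 5% vs 15% | 10.5% |
| 20% vs 60% | 1/10, 1/10 | 2% vs 6% | 0.8% |

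Equal attribution in both arms dilutes the contrast. Attribution that differs by arm can push it either way: 12% is below, and 78% above, the 29% for all events. The 78% is not a gain in sensitivity, because the same mechanism produces false signals. With no true difference (30% in both arms), no placebo events attributed and half of FMT events attributed, the analysed rates are 0% and 15%, and the test rejects about 24% of the time.

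**What is counted without attribution.**

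| Counted whatever the cause | Only through the filtered endpoint |
|---|---|
| Blood stream infection (positive culture) | Infections without a positive blood culture |
| Fever | Gastrointestinal harms other than diarrhoea |
| Severe diarrhoea to 3 weeks | Gastrointestinal events after 3 weeks |
| | Other organ toxicity |

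The left column comes from the primary and secondary outcome lists. The objectives table files these under efficacy and clinical impact, not safety.

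**The case against.** The strongest reply is that the trial would not be blind to the harms of most interest. Blood stream infection, fever and severe diarrhoea to 3 weeks are outcomes in their own right, as are antibiotic use, parenteral nutrition and length of stay. This stands. A reader might infer that an excess of infection or diarrhoea would go unseen altogether; the document does not support that.

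A reader might also infer that the Stage 1 review sees only attributed events. It does not: the Trial design section has the committee review outcomes and reported AEs, and it reviews AE data quarterly. Only the Stage 2 test and the stopping discretion are tied to the filtered term.

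Nor does the text show that placebo participants' events can never be called product-related, since those rescued with FMT have been exposed. It does not say that attribution is generally unblinded: events before the endpoint, and about 47% of participants, are unaffected. It does not give the supplier control of attribution, since supplier attendance is optional. Whether supplier members should vote is a governance preference, separate from this point.

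The SAE wording in the analysis section can be read as covering all SAEs. That would soften the problem without removing it, because non-serious AEs would still be filtered.

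Finally, tabulation detail may be left to an unseen analysis plan. That would answer a missing table. It does not answer a definition and a test that the article itself fixes.

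**Conclusion.** The point holds for the safety endpoint. As written, it measures attribution to the product rather than incidence after dosing, and the plan states no all-cause AE comparison by arm. The definition is used consistently from Stage 1 into the Stage 2 analysis, so it is not a slip of wording.

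The loss is real for events with no separate outcome, the right-hand column of the second table. Its size cannot be derived from the document: the power figures rest on assumed event rates and attribution fractions, and the drop from 29% to 4% holds only for equal one-in-four attribution. The 53% rests on the plan's own rates.

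The correction would not turn a trial of 51 into one that reliably detects moderate harm. A true 30% versus 50% would still be missed about 71% of the time on all events. What it restores is a comparison protected by randomisation.

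**What to change.** - Define a TE-AE as any AE that starts or worsens after the first capsule within the AE window already stated, whatever the cause.
- In Stage 2, compare all TE-AEs, grade 3 or higher AEs and SAEs by randomised arm. Show placebo participants' events before and after rescue FMT separately.
- Report product-related events, including possibly related ones, as a secondary subset, judged from listings that hide allocation.
- Reword the SAE part of the analysis sentence so that it is clear whether all SAEs are meant.
- The stopping discretion uses the same term, so the sponsor should state what it means there once the definition changes.

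The cost is mostly wording. AEs are already collected daily for in-patients and weekly after discharge, graded by CTCAE, and N stays at 51. Preparing listings that hide allocation adds some work. The downside is that reported AE rates will look higher in both arms, which the report should explain as the background toxicity of transplantation.
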